## 6.5. Monitoring plan

The investigators have a certificate of "Good Clinical Practice".

[figure not shown][figure not shown]

Hereby Certifies that  

## 7. Statistical design and analysis

### a) Analysis population

The entire population enrolled in the study will be included in the analysis.

### b) Descriptive statistics of baseline data

#### *Functional performance testing*

A mixed model will be constructed enabling within and between group (i.e., type of prosthesis) comparison of balance performance and accounting for baseline covariates. If residuals are not normally distributed, required adaptations to the data or model will be performed. To correct for multiple comparisons, suited corrections will be applied. The factors age, time since amputation, side of amputation, level of amputation, time using prosthesis, previously used prosthesis will be accounted for. Statistical significance level will be set at 5%.

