### d) Primary and secondary hypotheses

The different hypotheses (H) are:

**H1** We hypothesise that people walking with the passive prosthesis (LUNARIS®) will be able to cover significantly more distance (i.e.,  $> 35$ m) during 6-min walking compared to people walking with their current prosthetic device [4][5]. Secondly, we expect that wearing the LUNARIS® will improve postural stability and improve movement patterns after 12 weeks compared to walking with the current ankle prosthesis [6][7][8]. Thirdly, we noticed based on anecdotal evidence that people walking with the LUNARIS® are able to descend stairs more naturally, like able-bodied people. We hypothesise that doing the rehabilitation with the LUNARIS® will help people descending stairs without the need of rolling over the edge of a step, and as a consequence, will reduce the number of falls.

**H2** Based on my literature review on brain neuroplasticity after a lower limb amputation, we hypothesise to discover differences in structural whole-brain networks between participants with the LUNARIS® and current prosthesis after 12 weeks. We assume that these differences in structural networks will be less pronounced among people wearing the LUNARIS® compared to people wearing the current

prostheses [9]. Furthermore, we expect that these disparities in brain structural connectivity will translate into a change in performance on the physical tests.

e) Risks and anticipated adverse device effects that are to be assessed

To date, no device deficiencies have been reported with the LUNARIS®. We are not yet able to give a concise summary of device deficiencies and thus not able to report any deficiency that might have led to a serious adverse event if appropriate action had not been taken, intervention had not occurred, or circumstances had been less fortunate.

The Risk Management File is attached to this document.

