##### Protocol:

Figure 2 provides a visualisation of the investigation workflow.

[figure not shown]

Figure 2: Overview clinical trial. MRI: Magnetic Resonance Imaging, PEQ: Prosthetic Evaluation Questionnaire, ADL: Activities of Daily Living

The clinical investigation will comprise 4 test days for participants with a lower limb amputation and 2 days for the control group of able-bodied individuals.

The able-bodied individuals will undergo an MRI-scan at the University hospital Brussels (dpt. Radiology and Magnetic Resonance) and then perform functional performance tests.

Participants with a lower limb amputation will start the clinical investigation upon the start of their rehabilitation. At week 0, when initiating the rehabilitation, participants will undergo a baseline MRI-scan at the University hospital Brussels (dpt. Radiology and Magnetic Resonance). Then, they will be allocated to the one of the treatment arms (LUNARIS® or the SACH® foot) and will conduct their rehabilitation to learn walking with a prosthesis. At the end of the rehabilitation, after 12 weeks, participants will perform baseline functional performance tests, fill out the prosthetic evaluation questionnaire (PEQ) measuring quality of life [11] and fill out the Mini-Mental State Examination to account for cognitive impairments and onset of Alzheimer's Disease [12]. Between weeks 12 and 24 of the clinical investigation (i.e. intervention period), participants will perform their daily activities with the allocated prosthesis. During this 12-week period, trying out new prosthetic devices will be allowed within the group of individuals wearing the SACH® foot as this is considered the usual care. At the end of this period (after week 24), post-test assessment will take place and participants will undergo the same MRI and functional performance tests as during the baseline assessments to evaluate the changes that occurred. Additionally, the participant will be asked to fill out the Quebec User Evaluation of Satisfaction with assistive Technology (QUEST 2.0) to assess prosthetic satisfaction [25-27]. The 12-week intervention period is chosen based on a study examining the effect of 12 weeks balance training in healthy and older adults on neuroplasticity and on the accommodation time to walking with a new prosthesis [13][14][15].

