## e) Equipment to be used for assessing the clinical investigation variables

### Functional performance testing

Functional balance will be examined. Table 2 lists the different tests. A 6-min walking test, dual-task L-test, L-test, slope walking test, and stairs climbing and descending test will indicate functional balance and dual-task performance. Rating of perceived exertion [16], level of fatigue and comfort [17] and NASA-Task Load index (NASA-TLX) assessing perceived workload [18] will be assessed after each task.

| Performance tests                       | Outcome                       | Materials                   |
|-----------------------------------------|-------------------------------|-----------------------------|
| Slope walking test [19]                 | Time to complete test         | Stopwatch                   |
|                                         | Biomechanical gait parameters | Inertial measurements units |
| Stair climbing and descending test [20] | Time to complete test         | Stopwatch                   |
|                                         | Biomechanical gait parameters | Inertial measurements units |
| Dual-task L-test [21]                   | Time to complete test         | Stopwatch                   |
|                                         | Accuracy of subtractions      | Audio-recorder              |
| L-test [21]                             | Time to complete test         | Stopwatch                   |
| 6-min walking test [5]                  | Distance covered in 6 minutes | Measuring wheel             |
|                                         | Biomechanical gait parameters | Inertial measurements units |

Table 2: Physical performance tests

The primary endpoint is the distance covered during the 6-min walking test. Any difference found between the different prostheses on the distance travelled will be considered clinically relevant from a difference of 35 metres [5]. Secondary endpoints will comprise performance on the L-test, dual-L-test, slope walking test and stairs climbing and descending test, and the evaluation of the gait pattern.

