### d) The significance level of the power of primary endpoint(s)

Statistical significance level will be set at 5%.

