### e) Sample size calculation and justification

The primary endpoint of the clinical trial is the distance covered during the 6-minutes' walk test. The sample size was calculated based on a study comparing passive and quasi-passive prosthetic ankles which found an effect size Cohens'  $f = 0.318$  on distance covered during the 6-minutes' walk test [4]. A total of 40 participants with a lower limb amputation is required and will be allocated to one of the two prosthetic groups. These individuals will be stratified by age (2 strata:  $< 45$  years,  $\geq 45$  years, block size = 4) to control for age-related cognitive deterioration. A matched control-group of 20 able-bodied individuals will be included to enable comparison. The required number of 40 participants with amputation is based on a sample size calculation for an analysis of variance using G\*Power (version 3.1.9.4) envisaging 10% drop-out. Values used for this calculation were medium expected effect size  $f = 0.318$ , power = 0.80,  $\alpha = 0.05$ , the number of groups = 3 and the number of measurements set at 2 with a correlation between measurements of 0.75.

- f) The rationale for the number of procedures to be performed by a single user as part of the learning curves

A baseline experiment with a conventional prosthetic ankle used in rehabilitation is required to observe any similarities or differences in outcomes with the LUNARIS®. Moreover, a baseline experiment with able-bodied subjects is required to observe any similarities or differences in outcomes with the LUNARIS®. Therefore, each lower-limb amputee is asked to schedule four appointments and each able-bodied subject is asked to schedule two appointments to run through the whole experiment.

- g) Pass / Fail criteria to be applied to the results of the clinical investigation

Not applicable.

- h) The provision for an interim analysis

Not applicable.

- i) Management of bias

All appointments for the MRI will take place at UZ Brussel to avoid any bias due to a different MRI scanner. All appointments for functional performance testing will take place at Axiles Bionics to avoid any bias due to different slopes or staircases between subjects and between sessions.

- j) Management of potential confounding factors

Not applicable.

- k) Description of procedures for multiplicity control and adjustment of error probabilities

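### The primary comparison of 6-minute walk distance is described both as a level difference between prostheses and as a week 12 to 24 change, and these answer different questions

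*Protocol*

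**What the plan says.** Section 6.1 e defines the outcome without a week or a contrast: "The primary endpoint is the distance covered during the 6-min walking test". The same section treats a 35 m difference between prostheses as clinically relevant. H1 in section 5 d is also a between-prosthesis statement: LUNARIS users "will be able to cover significantly more distance" than people on their current device. Its walking-distance sentence names no week.

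The workflow in section 6.1 d is framed differently. The first walking test comes at week 12: "At the end of the rehabilitation, after 12 weeks, participants will perform baseline functional performance tests". By then participants have rehabilitated for 12 weeks on the foot allocated at week 0. At week 24, "participants will undergo the same MRI and functional performance tests as during the baseline assessments to evaluate the changes that occurred".

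Section 7 b describes one mixed model, "enabling within and between group (i.e., type of prosthesis) comparison of balance performance and accounting for baseline covariates"; section 6.1 e counts the walk test among the balance tests. Section 7 b also promises suitable corrections for multiple comparisons, without naming a method or a family. Section 7 d sets 5%. Section 7 e sizes an analysis of variance with "the number of groups = 3 and the number of measurements set at 2 with a correlation between measurements of 0.75" but does not say which effect is powered. Section 5 a gives the study's purpose as comparing rehabilitation with LUNARIS against rehabilitation with usual rigid passive feet.

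**The concern.** Level and change are not two routes to the same answer here. In many pre/post trials the first measurement precedes the intervention, so change from baseline and the final difference estimate the same effect. In this trial the measurement called baseline is taken after half of the 24-week exposure, and that half is the rehabilitation phase the study is about.

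A benefit acquired in rehabilitation and then maintained is present at both visits. It appears in full in a week-24 difference and vanishes from a week 12 to 24 change. If the week-12 distance were one of the baseline covariates in the section 7 b model, most of the benefit would be adjusted away as well. The same data could then support H1 under section 5 d and fail to support it under section 6.1 d.

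**Working it through.** **1. Can the sample size show which effect was meant?** Inputs from section 7 e: f = 0.318 (f² = 0.1011), 3 groups, m = 2 measurements, ρ = 0.75, α = 0.05, power 0.80, 10% drop-out, stated result 40 amputees.

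- Between effect: λ = f²·N·m/(1 + (m−1)ρ) = 0.1011·N·2/1.75. Power first reaches 0.80 at N = 87. Two of the three groups hold 58, and 58/0.9 = 64.4, so 65 amputees.
- Group-by-time effect: λ = f²·N·m/(1−ρ) = 0.1011·N·2/0.25. N = 16, or 18 if balanced. Two groups hold 12, and 12/0.9 = 13.3, so 14 amputees.
- Within effect: N = 13, or 15 if balanced. Two groups hold 10, and 10/0.9 = 11.1, so 12 amputees.

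None of these gives 40. At α = 0.05 with three groups, only an unstated correlation of 0 comes near (38 amputees). The calculation therefore does not reveal the intended comparison. The able-bodied group is also measured only once (section 6.4 a), so 3 groups by 2 measurements does not match the schedule.

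**2. What each contrast detects.** Assumptions: f = 0.318 read as a two-arm effect, so d = 2f = 0.636 SD; this advantage is present at week 12 and unchanged at week 24; 20 per arm; ρ = 0.75; two-sided 5% (the protocol does not state sidedness).

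| Contrast | Expected arm difference | Share of trials significant |
|---|---|---|
| Week-24 level | 0.636 SD; noncentrality 0.636·√(20/2) = 2.01 against a critical t of 2.02 | about 0.50 |
| Week 12 to 24 change | 0.636 − 0.636 = 0 | about 0.05, the test's own error rate |
| Week 24 adjusted for week-12 distance | 0.636·(1 − 0.75) = 0.159 SD; residual SD √(1 − 0.75²) = 0.661; ratio 0.24; noncentrality 0.24·√10 = 0.76 | about 0.11 |

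The change removes all of a stable benefit. Adjustment for the week-12 distance removes three quarters of it.

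**3. Error rate if the choice is left open.** With no device effect and no correction, the chance that the week-24 or the change contrast reaches 5% is about 0.095 by simulation (20 per arm, ρ = 0.75). The reference for two independent tests is 1 − 0.95² = 0.0975. Counting only results in favour of LUNARIS, the figure is about 0.048 against a reference of 0.025.

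**4. Power once the week-24 difference is fixed.** With d = 0.636 and no adjustment, power is 0.46 with 36 evaluable amputees (18 per arm, noncentrality 0.636·√9 = 1.91) and 0.50 with 40. Section 7 e states 0.80.

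**The case against.** The strongest reply is that the text describes one ordinary pre/post design. Week 12 is labelled baseline, week 24 post-test and the interval the intervention period, H1's next sentence speaks of effects after 12 weeks, and the sample size uses two correlated measurements. The exact contrast could then be left to a statistical analysis plan. The labels do fit that reading, but it conflicts with section 5 a and with the workflow itself, which allocates the foot at week 0. An analysis plan may set out model details; it cannot reconcile two different primary questions stated in the protocol.

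A second reply is that baseline adjustment is desirable because section 6.3 e calls the study non-randomised. That holds for variables measured before allocation. The week-12 distance is not one of them. Section 7 b does not list it among the factors to be accounted for either, so its use as a covariate is a risk in the wording and not a stated plan.

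Stronger readings are tempting and should be resisted.

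- A reader might infer that a benefit may be claimed from whichever test reaches 5%. Section 7 b promises corrections, so the text does not permit this. The promise is unspecific and would not prevent a single contrast being chosen late, but the uncorrected rates are upper bounds and not the plan's error rate.
- A reader might infer that a within-arm gain could decide H1. No passage says so: RO.1.1, H1 and the 35 m threshold all compare prostheses, and section 7 b only says the model enables within-group comparison.
- A reader might count further tests and reach 0.12 (adding the week-12 difference) or 0.15 (adding the within-LUNARIS test). No passage proposes a week-12 difference, or an average over visits, as primary. With plain Bonferroni the three-contrast figure falls to about 0.04.

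**Conclusion.** The point holds as a conflict in stated text: a between-prosthesis level difference without a week in sections 5 d and 6.1 e, against a change from a post-allocation baseline in section 6.1 d, with baseline covariates in section 7 b that leave room for either.

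The main consequence is for what the trial can detect. A stable benefit is found about half the time by one contrast and only at the chance rate by the other. The inflation of type I error is secondary, at most about 0.10 for the two contrasts the text suggests.

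The detection figures rest on reading f = 0.318 as a two-arm effect, on an advantage that is constant across visits, and on the protocol's correlation of 0.75. The direction of the conflict does not depend on these values. It should be settled before data are seen.

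**What to change.** In sections 5 d, 7 b and 7 d, name one primary test: the LUNARIS minus usual-care difference in mean 6-minute walk distance at week 24, estimated from the mixed model and tested two-sided at 5%. Week 24 is the post-test and the end of the full exposure period, so it fits H1 and section 5 a. Also state that:

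- the week-12 distance is an outcome measured after allocation and is not a baseline covariate;
- the week-12 difference and the group-by-time term are supportive and cannot replace the primary test;
- within-arm changes and comparisons with the able-bodied group are descriptive;
- the promised multiplicity corrections apply to the secondary endpoints.

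In sections 5 c and 7 e, say which effect is powered and restate the power for this contrast.

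The wording costs a few sentences and no new visits or data. There are two real costs. A benefit seen only at week 12, or only as a change, can no longer be the primary result. The protocol must also acknowledge that 36 to 40 amputees give about 0.46 to 0.50 power unadjusted, under the assumption above, and not 0.80. Adjustment for covariates measured before allocation could raise this. Otherwise the sponsor must revise the sample size or accept the lower power openly.

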## 1.5. Overall synopsis of the clinical investigation

|                    |                                                                                                                                                                                          |
|--------------------|------------------------------------------------------------------------------------------------------------------------------------------------------------------------------------------|
| Official title     | Human-Prosthetic Interaction: Brain & Technology After Lower-Limb Loss                                                                                                                   |
| Objectives         | The main objective of this investigation is to compare rehabilitation with the LUNARIS® and with usual rigid passive feet.                                                               |
| Endpoints          | Evaluating functional performance and structural brain adaptations when doing rehabilitation with an articulated ankle-foot prosthesis in comparison with a non-articulation prosthesis. |
| Study population   | Healthy people with lower-limb amputation                                                                                                                                                |
| Number of subjects | 40 lower-limb amputees                                                                                                                                                                   |

|                                    |                                                                                                                                                                                                                                                    |
|------------------------------------|----------------------------------------------------------------------------------------------------------------------------------------------------------------------------------------------------------------------------------------------------|
|                                    | 20 able-bodied persons                                                                                                                                                                                                                             |

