### f) The populations and indications for which the investigational device is intended.

The LUNARIS® is indicated for use as a component in a lower limb prosthesis for individuals with a missing lower-limb, for example due to trauma, vascular disease, cancer or congenital deficiency, including:

- Unilateral or bilateral amputation or deficiency
- Unilateral or bilateral knee disarticulation
- Unilateral or bilateral transfemoral amputation or deficiency
- Unilateral hip disarticulation

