#### d) Methods and timing for assessing, recording and analysing variables

##### Population & sample size:

Adults aged 25-65 with a transtibial amputation will be recruited through contacting rehabilitation centres, and orthopaedic departments of hospitals within the network of BruBotics ([BruBotics.eu](https://BruBotics.eu)) and Axiles Bionics ([Axiles Bionics | Next Generation Bionics](https://AxilesBionics.com)). Adults with a Medicare Functional Classification level lower than K3, metal implants, bilateral amputation, additional upper-limb amputation or diabetes will be excluded as well as participants with neurological disorders or with excessive stump pains and wounds. All participants will be asked to provide their written consent after being written and verbally informed regarding the study protocol. The study will be executed in compliance with the Declaration of Helsinki [10] and Ethical approval will be sought from the medical ethics commission of VUB and UZ Brussel.

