## 6.3. Subjects

### a) Inclusion criteria for subject selection

- Age: 25 - 65 years
- Gender: men and women
- Level of amputation: unilateral transtibial
- Medicare Functional Classification Level: K3-K4

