### b) Exclusion criteria for subject selection

- Having metal implants
- Bilateral or additional upper-limb amputation
- Diabetic cause of amputation
- Neurological disorders
- Excessive stump pains and wounds

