#### *Structural brain adaptations*

Differences in connectivity between pre-test and post-test assessment, both within and between groups (i.e. type of prosthesis), will be analysed by means of structural equation modelling. This analysis allows to investigate the causal relationships between brain structure and performance indicators while controlling for confounding factors. The factors time since amputation, side of amputation, amputation level, time using prosthesis, previously used prosthesis, age, sex, Mini-Mental State Examination score, and level of education will be accounted for. Statistical significance level will be set at 5%.

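### Both covariate lists omit cause of amputation, which eligibility leaves mixed and allocation does not balance, so an uneven mix could bias the 6-minute-walk comparison between arms

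*Protocol*

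**What the plan says.** **Covariates.** Section 7 b) fixes an explicit list for each analysis. Functional tests: "The factors age, time since amputation, side of amputation, level of amputation, time using prosthesis, previously used prosthesis will be accounted for". Brain networks: "time since amputation, side of amputation, amputation level, time using prosthesis, previously used prosthesis, age, sex, Mini-Mental State Examination score, and level of education". Cause of amputation is in neither.

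**Eligibility.** Inclusion is by age, sex, K3-K4 and "Level of amputation: unilateral transtibial". The only criterion that concerns cause is the exclusion "Diabetic cause of amputation" in section 6.3 b). Section 6.1 d) words it differently: "additional upper-limb amputation or diabetes will be excluded". The two wordings should be reconciled, but neither touches any other cause. Section 2 f) describes intended device users as people missing a limb "for example due to trauma, vascular disease, cancer or congenital deficiency". That is the device indication, not the trial's entry list. The synopsis describes the population as "Healthy people with lower-limb amputation".

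**Allocation and confounding.** Section 6.3 e) says the study is not randomised. Sections 5 c) and 7 e) describe two age strata with a block size of 4, which reads like randomisation. Sections 7 j) and 7 n) mark confounding management and sensitivity analysis as not applicable. Section 6.4 c) recognises no factor that could compromise the outcome, and section 6.4 d) relies on the entry criteria.

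**Reference figure.** Section 6.1 e) treats a difference between prostheses as clinically relevant from 35 m on the 6-minute walk.

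**The concern.** When allocation is not randomised, covariate adjustment is the main protection for the device comparison. The reason for the amputation can plausibly affect walking capacity whatever foot is worn, because vascular or other systemic disease limits walking in a way that an injury does not. The entry criteria leave the mix of causes open, no stratum balances it, and the model does not adjust for it. If one arm receives more traumatic amputees than the other, part of the difference in distance belongs to the patients and not to the foot.

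Both lists meanwhile include level of amputation, which is the same for every participant and so adjusts for nothing.

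**Working it through.** **1. What balances or adjusts for cause**

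| Possible safeguard | Where | Does it cover cause? |
|---|---|---|
| Entry criteria | 6.1 d), 6.3 a), 6.3 b) | Only the diabetic cause (or diabetes) is removed |
| Allocation | 6.3 e); 5 c) and 7 e) | No: not randomised, or in blocks within age strata |
| Covariates | 7 b) | No. Age is a partial proxy; level is constant |
| Confounding, sensitivity analysis | 7 j), 7 n) | Marked not applicable |

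**2. Size of the shift at one time point**

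The plan gives no figure for the cause mix, the walking gap between causes or the standard deviation (SD), so there is no plan figure to reproduce. All three are assumptions. From the plan: 20 per arm and the 35 m threshold.

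Shift in the arm difference = (difference in the share of the poorer-walking cause) x (gap in distance between causes).

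- 20-point imbalance, 40 m gap: 0.20 x 40 = 8 m, or 8/35 = 23% of the threshold.
- 20-point imbalance, 120 m gap: 0.20 x 120 = 24 m, or 24/35 = 69%.

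Gap needed to produce the full 35 m: 35/0.20 = 175 m, 35/0.30 = 117 m, 35/0.40 = 88 m.

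**3. Systematic imbalance, no true device effect**

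Simulation: 20 per arm, SD 90 m within cause (assumed), 8,000 runs per setting, linear model for a single time point with arm alone or arm plus cause, tested at 5%.

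| Share of poorer-walking cause, device / comparator | Gap (m) | Cause omitted: mean estimate (m), rejection | Cause included: mean estimate (m), rejection |
|---|---|---|---|
| 20% / 40% | 50 | 10.0, 6.0% | -0.2, 5.4% |
| 20% / 40% | 100 | 19.8, 9.1% | 0.0, 4.7% |
| 20% / 40% | 150 | 30.0, 13.1% | 0.1, 5.3% |
| 15% / 45% | 50 | 15.3, 7.9% | 0.6, 4.9% |
| 15% / 45% | 100 | 30.3, 15.8% | -0.2, 4.6% |
| 15% / 45% | 150 | 44.8, 24.6% | -0.2, 5.0% |
| 10% / 50% | 50 | 19.9, 10.5% | 0.0, 5.1% |
| 10% / 50% | 100 | 40.2, 24.6% | -0.4, 5.1% |
| 10% / 50% | 150 | 60.9, 40.2% | 0.5, 4.8% |

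**4. Change contrasts**

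Let the gap between causes be g12 at week 12 and g24 at week 24, and the imbalance be d. The between-arm difference at week 24 carries d x g24. The between-arm difference in change carries d x (g24 - g12), which is zero if the gap is stable. The same algebra applies to the MRI: section 6.1 d) puts the first scan at week 0, before allocation, and section 7 b) analyses pre-post differences in connectivity.

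For the walk test the plan does not fix which contrast is primary. H1 in section 5 d) is a between-group comparison of distance. The first walk test comes after 12 weeks of rehabilitation on the allocated foot, so the week 12 value is not a pre-allocation baseline. The level contrast is thus a live reading of the plan.

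**5. Cost in precision**

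At a standardised difference of 0.91, which gives 80.1% power with 20 per arm and no covariates, power is 79.7% with six one-degree-of-freedom covariates and 79.6% with seven.

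**The case against.** The strongest reply has four parts.

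- **Stable differences cancel.** In a week 12 to 24 change, or in the pre-post MRI contrast, a constant difference between causes drops out. This stands. A reader might infer that the MRI comparison is biased outright; the documents do not support that, because the first scan precedes allocation and the analysis is of change.
- **Chance imbalance is not bias.** If 8 to 16 of the 40 were non-traumatic, a purely random 20/20 split would differ by at least 20 points in 24% to 33% of allocations. The standard error already allows for that. This stands too: those percentages are not a probability of confounding. Nothing in the protocol says that cause would drive device assignment, and the age strata with block size 4 conflict with the statement that allocation is not randomised. Until that is reconciled, whether an imbalance would be systematic is open. Neither version balances cause.
- **Age, K3-K4 and the description of the population as healthy narrow the gap.** In part. Age is in both models and K3-K4 limits the range of walking ability, so the gap that remains after adjustment may be smaller than assumed. Neither is a criterion on cause.
- **Cause may not be on file.** A reader might infer that screening already establishes it for everyone. Strictly, the entry criteria need only diabetic versus non-diabetic status, so the traumatic/non-traumatic item has to be added.

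It may also be said that an analysis plan could add the covariate. The protocol, however, names the lists and declares confounding not applicable, so the omission is fixed in the text.

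**Conclusion.** The point holds as a bounded risk. The protocol compares two arms of 20, stated as non-randomised, with a plausible confounder left out of both covariate lists and no other provision for it. At a single time point, a 20-point imbalance and a 40 to 120 m gap shift the walk comparison by 8 to 24 m. For the change in walk distance and for the MRI contrast, there is bias only if cause alters the trajectory.

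The tempting stronger reading is that an uneven mix would by itself pass for a clinically relevant device effect. The figures do not carry that: reaching 35 m takes a 175 m gap at 20 points, or a larger imbalance together with a gap of about 117 m (30 points) or 88 m (40 points). The gap, the mix and the SD are all assumptions, not taken from the documents.

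This is a cheap improvement to consider, with moderate confidence.

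**What to change.** 1. Record cause of amputation at screening as traumatic or non-traumatic.
2. Tabulate it by arm with the baseline data.
3. In section 7 b), replace level of amputation with cause of amputation in both the functional and the brain-network model.
4. In section 7 j), replace the not-applicable entry with a statement that cause is handled by this adjustment.

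Separately, reconcile section 6.3 e) with the strata and block size in sections 5 c) and 7 e), and the two wordings of the diabetes exclusion.

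The cost is one recorded item, a protocol wording change and at most about one degree of freedom, or roughly 0.1 percentage point of power in the example above. If nearly everyone falls into one category, the table will show it and little is lost.
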